## Abstract

**Background:**

Pain-dominant shoulder periarthritis is characterized by shoulder pain, restricted range of motion (ROM), and impaired daily function. Electroacupuncture (EA) is a controllable acupuncture modality used for shoulder pain disorders; however, direct evidence comparing 2 Hz and 100 Hz EA in this disease stage remains limited.

**Objective:**

This study aims to compare the efficacy and safety of low-frequency EA (2 Hz) and high-frequency EA (100 Hz) for pain-dominant shoulder periarthritis.

**Methods:**

This is a single-center, participant- and outcome assessor-blinded, parallel-group randomized controlled trial (RCT) to be conducted at the Third Clinical Hospital Affiliated to Changchun University of Chinese Medicine. A total of 152 participants who meet the diagnostic criteria for pain-dominant shoulder periarthritis and the traditional Chinese medicine (TCM) meridian differentiation criteria for the Hand Shaoyang meridian pattern will be enrolled. Participants will be randomly assigned in a 1:1 ratio to the 2 Hz EA group or the 100 Hz EA group. Both groups will receive the same acupuncture prescription, treatment procedures, and co-interventions, with EA frequency as the only planned between-group difference. Treatment will be administered once daily for 5 consecutive days per course, with a 2-day interval between courses, for a total of 10 sessions. Outcomes will be assessed at baseline and at 2, 8, and 24 weeks after treatment initiation. The primary outcome will be overall shoulder pain intensity measured using a 10-cm visual analog scale (VAS) at T1. The primary comparison will be the adjusted mean difference in the T1 overall VAS score between the two groups, with baseline overall VAS included as a covariate. Secondary outcomes will include component-specific VAS ratings for resting pain, activity-related pain, and nocturnal pain, the Shoulder Pain and Disability Index (SPADI), the Constant-Murley Score (CMS), and shoulder ROM. Adverse events (AEs) and serious adverse events (SAEs) will be recorded throughout the study.

**Discussion:**

This trial may provide clinical evidence to inform EA frequency selection and parameter standardization for pain-dominant shoulder periarthritis.

**Clinical trial registration:**

International Traditional Medicine Clinical Trial Registry, https://itmctr.ccebtcm.org.cn, identifier ITMCTR2026000862.

## Introduction

1

Shoulder periarthritis, also known as frozen shoulder or adhesive capsulitis, is a common shoulder disorder characterized by shoulder pain, restricted active range of motion (AROM) and passive range of motion (PROM), and shoulder-related functional impairment (1). The main pathological processes include capsular inflammation, fibrosis, adhesion, and contracture, which can reduce joint cavity volume and limit shoulder mobility (2).

The disease usually follows a staged clinical course and is commonly described as progressing through a pain-dominant stage, a stiffness stage, and a recovery stage. The pain-dominant stage is mainly characterized by resting pain, nocturnal pain, and activity-related pain, and may also involve a rapid decline in shoulder ROM. These symptoms can substantially affect sleep and daily activities, such as dressing, combing hair, reaching overhead, and shoulder abduction (3). Therefore, treatment at this stage should focus on prompt pain relief, preservation of tolerable shoulder movement, and prevention of persistent functional limitation.

Current conservative treatments for shoulder periarthritis include oral analgesic and anti-inflammatory medications, physical therapy, range-of-motion exercises, and rehabilitation interventions (4). For patients with prominent pain or more severe functional limitation, local corticosteroid injection, hydrodilatation, or other interventional treatments may also be considered (5). These approaches can relieve pain and improve shoulder mobility in the early stage. However, uncertainty remains regarding the optimal timing, treatment combinations, patient responses, and individual suitability of different interventions. Pharmacological and injection-based treatments may also be limited by injection-related discomfort, potential adverse effects, and patient acceptability (6). Therefore, a safe, reproducible, and standardized non-pharmacological treatment strategy is still needed.

Acupuncture is widely used as a non-pharmacological therapy for pain conditions (7). For shoulder periarthritis and related shoulder pain disorders, acupuncture may reduce pain and improve function through multiple mechanisms, including modulation of pain signaling, neurotransmitter activity, inflammatory responses, and peripheral or central sensitization (8). Electroacupuncture combines traditional acupuncture with electrical stimulation delivered through needles inserted at selected acupoints. Compared with manual acupuncture, EA allows better standardization of stimulation frequency, waveform, intensity, and treatment duration (9). This feature makes EA suitable for evaluating the relationship between stimulation parameters and clinical effects.

Previous studies have suggested that EA may relieve shoulder periarthritis-related pain compared with manual acupuncture or sham controls (10, 11). Randomized trials have also indicated that EA may reduce pain and improve shoulder function or mobility in patients with frozen shoulder (11, 12). Its overall safety profile appears acceptable, with few serious AEs reported (13). With the accumulation of evidence on acupuncture for shoulder pain (14), relevant evidence-based guidelines have recommended acupuncture for reducing pain intensity and improving shoulder ROM at appropriate clinical stages (15).

Among EA parameters, stimulation frequency is a key and quantifiable variable. Different frequencies may produce analgesic effects through distinct neurochemical and pain-modulatory mechanisms (16). Low-frequency EA is generally considered to be associated with the release of endogenous opioid peptides involving *μ*- and *δ*-opioid receptor pathways, whereas high-frequency EA may involve *κ*-opioid receptor pathways and spinal pain modulation (17). On this basis, 2 Hz and 100 Hz are commonly used as representative low- and high-frequency stimulation patterns, respectively (18–20).

However, direct evidence from RCTs comparing 2 Hz and 100 Hz EA remains lacking in shoulder periarthritis, especially in the pain-dominant stage. Existing studies have mainly compared EA with manual acupuncture, usual care, or sham controls. The specific question of which frequency is more suitable for pain-dominant shoulder periarthritis has not been adequately addressed.

Accordingly, this study was designed as a single-center, participant- and outcome assessor-blinded, parallel-group RCT. It aims to compare the efficacy and safety of 2 Hz and 100 Hz EA for pain-dominant shoulder periarthritis. Pain intensity will be assessed as the primary outcome. Shoulder pain and disability, overall shoulder function, and shoulder ROM will be evaluated as secondary outcomes. This trial is expected to clarify potential differences between low- and high-frequency EA in early pain relief, functional improvement, and sustained treatment effects during follow-up. The findings may provide evidence to inform EA frequency selection and parameter standardization for pain-dominant shoulder periarthritis.

## Methods and analysis

2

### Study design

2.1

This is a single-center, participant- and outcome assessor-blinded, parallel-group RCT. The trial aims to compare the analgesic effects, functional benefits, and safety of low-frequency EA (2 Hz) and high-frequency EA (100 Hz) in patients with pain-dominant shoulder periarthritis. Participant recruitment and treatment will be conducted at the Third Clinical Hospital Affiliated to Changchun University of Chinese Medicine from March 2026 to October 2026. Follow-up and data collection will continue until the last participant completes the T3 assessment. A total of 152 eligible participants will be recruited and randomly assigned in a 1:1 ratio to the low-frequency EA group (2 Hz; *n* = 76) or the high-frequency EA group (100 Hz; *n* = 76).

Four assessment time points will be used in this trial: T0 (baseline/before randomization), T1 (end of treatment, 2 weeks after treatment initiation), T2 (short-term follow-up, 8 weeks after treatment initiation), and T3 (medium-term follow-up, 24 weeks after treatment initiation). Outcomes related to pain, shoulder function, and shoulder ROM will be collected at each assessment time point. Adverse events and SAEs will be recorded throughout the trial. The primary outcome will be overall shoulder pain intensity measured using a 10-cm VAS at T1. The primary comparison will be the adjusted mean difference in the T1 overall VAS score between the two groups, with baseline overall VAS included as a covariate. Secondary outcomes will include component-specific VAS ratings for resting pain, activity-related pain, and nocturnal pain, the SPADI, the CMS, and shoulder ROM. ROM will include AROM and PROM. Table 1 summarizes the schedule of enrollment, interventions, and assessments. Figure 1 shows the study flowchart.

**Table 1 tab1:** Schedule of enrolment, interventions, and assessments.

Study phase	Screening period	T0	Treatment period	T1	T2	T3
Participant recruitment	×					
Pre-screening	×					
Informed consent	×					
Eligibility screening	×					
Western medical diagnostic criteria assessment	×					
TCM meridian differentiation assessment	×					
Inclusion/exclusion criteria review	×					
Medical history and physical examination	×					
Standard shoulder radiography and mandatory diagnostic ultrasonography	×					
Re-verification of pain-dominant status, including resting and nocturnal pain	×	×				
Baseline demographic data		×				
Baseline disease-related data		×				
Randomization		×				
Low-frequency EA group (2 Hz)			×			
High-frequency EA group (100 Hz)			×			
TDP irradiation			×			
VAS		×		×	×	×
Component-specific VAS ratings: resting, activity-related, and nocturnal pain		×		×	×	×
SPADI		×		×	×	×
CMS		×		×	×	×
Shoulder ROM (AROM/PROM)		×		×	×	×
Acupuncture sensation scale/sensation record			After each session			
EA device output level and within-session adjustment records			After each session			
Blinding success assessment				×		
Concomitant treatment records		×	Continuous	×	×	×
Rescue analgesic use records		×	Continuous	×	×	×
AE/SAE records		×	Continuous	×	×	×
Adherence and protocol deviation records			Continuous	×	×	×

× indicates that the item will be performed or assessed at the corresponding time point. Treatment period refers to weeks 1–2 after treatment initiation. T1, T2, and T3 refer to the end of treatment, 8 weeks after treatment initiation, and 24 weeks after treatment initiation, respectively. “After each session” indicates that the acupuncture sensation scale or sensation record will be completed after each treatment session. “Continuous” indicates ongoing recording from randomization to the final follow-up when applicable. Treatment consists of 10 sessions: once daily, 5 consecutive sessions per course, with a 2-day interval between courses. AE, adverse event; AROM, active range of motion; CMS, Constant–Murley Score; EA, electroacupuncture; PROM, passive range of motion; ROM, range of motion; SAE, serious adverse event; SPADI, Shoulder Pain and Disability Index; T0, baseline/before randomization; T1, end of treatment/2 weeks after treatment initiation; T2, 8 weeks after treatment initiation; T3, 24 weeks after treatment initiation; TCM, traditional Chinese medicine; TDP, specific electromagnetic spectrum lamp; VAS, Visual Analog Scale.

**Figure 1 fig1:**
[figure not shown]
Study flow diagram. Values marked as “TBD” will be recorded during the trial and reported after trial completion. EA, electroacupuncture; FAS, full analysis set; PPS, per-protocol set; SS, safety set.

This study protocol follows the Standard Protocol Items: Recommendations for Interventional Trials (SPIRIT) 2025 reporting guideline (21), and the completed SPIRIT 2025 checklist is provided as Supplementary Material 1. Details of the acupuncture intervention will be reported with reference to Standards for Reporting Interventions in Clinical Trials of Acupuncture (STRICTA) (22). The trial will be conducted in accordance with the Declaration of Helsinki and relevant ethical requirements for clinical research. All candidate participants will be fully informed of the study purpose, trial procedures, potential benefits and risks, data confidentiality measures, and their right to withdraw before participation. Written informed consent will be obtained voluntarily from each participant. The study protocol has been approved by the Medical Ethics Committee of the Third Clinical Hospital Affiliated to Changchun University of Chinese Medicine (approval No. CZDSFYLL2025-030-01). The trial has been registered with the International Traditional Medicine Clinical Trial Registry (registration No. ITMCTR2026000862; https://itmctr.ccebtcm.org.cn).

### Diagnostic criteria

2.2

The diagnostic criteria in this trial include Western medical diagnostic criteria for shoulder periarthritis and TCM meridian differentiation criteria. All participants must meet the Western medical diagnostic criteria for pain-dominant shoulder periarthritis and the meridian differentiation criteria for the Hand Shaoyang meridian pattern.

#### Western medical diagnostic criteria

2.2.1

The Western medical diagnostic criteria for shoulder periarthritis are based on classic descriptions of frozen shoulder (23), the consensus definition of frozen shoulder (1), and relevant clinical practice guidelines (3). Participants who meet the following criteria will be diagnosed with pain-dominant shoulder periarthritis:Pain is present in the affected shoulder. The main manifestations include resting pain, nocturnal pain, or activity-related pain. The pain may gradually worsen or recur over time;Both active and PROM are limited in the affected shoulder. The limitation involves at least two movement directions. Commonly affected directions include external rotation, abduction, forward flexion, and extension;Pain and restricted movement lead to reduced shoulder function. Daily activities may be affected, including dressing, combing hair, reaching overhead, shoulder abduction, shoulder extension, or sleep;Pain, rather than stiffness, is the predominant clinical manifestation and is accompanied by reduced shoulder ROM. At formal screening and again at the baseline visit before randomization, the participant must report active resting pain or nocturnal pain during the preceding 24 h, with at least one of these pain components rated ≥3 cm on a 10-cm VAS. Patients whose current clinical presentation is dominated by stiffness and mechanical restriction without active resting or nocturnal pain will not be considered to have pain-dominant shoulder periarthritis;Standard shoulder radiography shows no fracture, dislocation, marked osteoarthritis, or other osseous structural lesion that could explain the current symptoms;Mandatory diagnostic ultrasonography of the affected shoulder shows no partial-thickness or full-thickness rotator cuff tear. Subacromial impingement syndrome, calcific tendinitis, cervicogenic shoulder pain, radiculopathy, tumor, infection, and other definite causes of shoulder pain are excluded on the basis of the medical history, physical examination, shoulder radiography, and diagnostic ultrasonography. Shoulder magnetic resonance imaging will be performed if the ultrasonographic findings are inconclusive or if additional structural pathology is suspected.

#### TCM meridian differentiation criteria

2.2.2

The TCM meridian differentiation criteria are based on the classification and treatment of Loujianfeng in Acupuncture Therapeutics, a national planning textbook for higher education in TCM during the Fourteenth Five-Year Plan period (24). This trial will include participants with the Hand Shaoyang meridian pattern. Participants who meet the following criteria will be identified as having the Hand Shaoyang meridian pattern:Pain is mainly located on the lateral or posterolateral side of the shoulder and may radiate along the lateral side of the upper arm;Obvious tenderness is present near Jianliao (SJ14) or along the pathway of the Hand Shaoyang meridian;Pain is aggravated during shoulder abduction, elevation, or external rotation, with corresponding movement limitation;Local soreness, distension, tightness, discomfort, or aggravation after exertion may be present;The Hand Shaoyang meridian pattern is determined by the study physician after a comprehensive assessment of medical history, pain location, tender point distribution, and characteristics of shoulder movement limitation.

### Inclusion criteria

2.3

Participants must meet all of the following inclusion criteria and none of the exclusion criteria listed in Section 2.4:They meet both the Western medical diagnostic criteria for pain-dominant shoulder periarthritis and the TCM meridian differentiation criteria for the Hand Shaoyang meridian pattern, as described in Section 2.2;They are 30–80 years of age, inclusive, regardless of sex;They have unilateral shoulder pain and restricted shoulder movement, with clear tender points around the affected shoulder;The disease duration is ≥4 weeks and <36 weeks. Because the timing of clinical stage transition varies among patients, eligibility will be determined according to the current clinical presentation rather than disease duration alone. Pain must remain the predominant clinical manifestation, and active resting pain or nocturnal pain must be present, with at least one of these components rated ≥3 cm on a 10-cm VAS at both formal screening and the baseline visit before randomization;The pain score on a 10-cm VAS is >3 at screening;Standard shoulder radiography shows no fracture, dislocation, marked osteoarthritis, or other osseous lesion that could explain the current symptoms, and mandatory diagnostic ultrasonography of the affected shoulder shows no partial-thickness or full-thickness rotator cuff tear or other clinically relevant soft-tissue lesion that could account for the presenting symptoms;They voluntarily agree to participate in the study and sign written informed consent, and are able to complete the treatment, outcome assessments, and follow-up procedures.

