Before any study-related procedure is performed, research staff will provide full information to each candidate participant. This information will include the study purpose, trial procedures, potential benefits and risks, alternative treatment options, data confidentiality measures, the right to withdraw, and protection of medical rights after withdrawal. Candidate participants will be given sufficient time to ask questions and consider participation. Individuals who voluntarily agree to participate will sign written informed consent and receive a unique study identification number. Participants who have signed informed consent and are confirmed as eligible will complete the baseline assessment before randomization. At the baseline visit and before randomization, the study physician will re-evaluate the participant’s current clinical stage. Pain-dominant status will be reconfirmed on the basis of the predominant clinical complaint and the presence and intensity of resting and nocturnal pain. Candidates whose symptoms have transitioned to a stiffness-dominant presentation or who no longer meet the pain-dominant criteria will not be randomized, and the reason for non-enrollment will be recorded in the screening log. Personal information will be used only for the purposes of this study and will be managed in a de-identified manner. Participants may withdraw from the study at any time without penalty. Reasons for withdrawal will be recorded in the screening, enrollment, and follow-up records when available.

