##### Visual analog scale

2.11.1.1

The primary outcome will be overall shoulder pain intensity measured using a 10-cm VAS (27). The left endpoint of the scale represents “no pain,” and the right endpoint represents “the worst possible pain.” Research staff will provide the following standardized instruction: “Considering all periods of rest, movement, and nighttime during the past 24 h, please mark on the line the overall average intensity of pain in your affected shoulder.” The distance from the left endpoint to the participant’s mark will be measured to the nearest millimeter and expressed as a score ranging from 0 to 10, with a higher score indicating more severe pain. A sample of the VAS and its standardized administration instructions are provided in Supplementary Figure S1.

The overall VAS will be assessed at T0 (baseline/before randomization), T1 (end of treatment, 2 weeks after treatment initiation), T2 (short-term follow-up, 8 weeks after treatment initiation), and T3 (medium-term follow-up, 24 weeks after treatment initiation). The primary comparison will be the adjusted mean difference in the T1 overall VAS score between the two groups, with baseline overall VAS included as a covariate. Changes from baseline at T1, T2, and T3 will also be reported as supportive descriptive and follow-up efficacy outcomes.

To facilitate clinical interpretation, an individual reduction of ≥1.4 cm from baseline on the 10-cm overall VAS will be considered a minimal clinically important improvement (28). In addition, a post-treatment overall VAS score of ≤3.0 cm will be used as a supportive threshold for the patient acceptable symptomatic state (28). The proportions of participants achieving these thresholds at T1 will be evaluated as supportive exploratory outcomes.

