The primary efficacy endpoint will be the T1 overall VAS score. The primary analysis will use an analysis of covariance model. The T1 VAS score will be used as the dependent variable, group will be included as a fixed factor, and baseline VAS score will be included as a covariate. The adjusted mean difference in T1 VAS score between the two groups will be reported with the 95% confidence interval and *p* value. Descriptive results for the change from baseline to T1 will also be reported. At T1, the proportions of participants achieving a reduction of ≥1.4 cm from baseline in the overall VAS and an overall VAS score of ≤3.0 cm will be summarized by treatment group. Between-group differences will be evaluated using the chi-square test or Fisher’s exact test, as appropriate. Risk ratios and risk differences will be reported with 95% confidence intervals. These responder analyses will be considered supportive and exploratory.

To evaluate treatment trends over time, linear mixed-effects models will be used for continuous repeated-measure outcomes, including the overall VAS, component-specific VAS ratings, SPADI, CMS, and ROM. The models will include group, time, group-by-time interaction, and the corresponding baseline value. Participant will be included as a random effect. Time will be treated as a categorical variable. An unstructured covariance structure will be preferred. If the model does not converge, an appropriate covariance structure will be selected according to model fit indices. The group-by-time interaction will be used to evaluate whether treatment trends differ between the two groups across time points. The between-group difference in the primary outcome at T1 will be the main focus. Between-group differences in changes from baseline at T2 and T3 will also be reported for each outcome.

The component-specific VAS ratings for resting pain, activity-related pain, and nocturnal pain will be analyzed as exploratory secondary outcomes. Between-group differences at T1 will be estimated using analysis of covariance with adjustment for the corresponding baseline pain score. Changes over time will be explored using linear mixed-effects models including group, time, group-by-time interaction, and the corresponding baseline value. Effect estimates and 95% confidence intervals will be reported, and these analyses will be interpreted as exploratory.

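### The two exploratory T1 responder outcomes are compared without baseline VAS, and a few participants may already meet the ≤3.0 cm state at entry

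*Protocol article*

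**What the plan says.** **Responder outcomes.** Section 2.11.1.1 sets two thresholds for clinical interpretation at T1: "an individual reduction of ≥1.4 cm from baseline on the 10-cm overall VAS will be considered a minimal clinically important improvement", and "a post-treatment overall VAS score of ≤3.0 cm will be used as a supportive threshold for the patient acceptable symptomatic state". Section 2.13 labels both analyses supportive and exploratory and fixes the method: "Between-group differences will be evaluated using the chi-square test or Fisher’s exact test, as appropriate", with risk ratios, risk differences and 95% confidence intervals. No covariate is named. The primary analysis in the same section is an ANCOVA of T1 overall VAS with baseline overall VAS as covariate.

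**Entry.** Section 2.3 requires "The pain score on a 10-cm VAS is >3 at screening" and does not say which of the protocol's four VAS ratings (overall, resting, activity-related, nocturnal) is meant. The pain condition repeated at baseline concerns resting or nocturnal pain, "with at least one of these components rated ≥3 cm on a 10-cm VAS at both formal screening and the baseline visit before randomization". Section 2.5 describes the check before randomisation: "Pain-dominant status will be reconfirmed on the basis of the predominant clinical complaint and the presence and intensity of resting and nocturnal pain". The overall VAS is a separate item with its own instruction: "Considering all periods of rest, movement, and nighttime during the past 24 h, please mark on the line the overall average intensity of pain". It is recorded at T0, but no section gives it a minimum there.

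**The concern.** Both responder outcomes are cut-points of T1 overall VAS or of its change from baseline, so a participant's chance of success depends on where he or she started. The primary model uses that information and the responder comparison does not. The risk ratios and differences are the figures most likely to be quoted to explain the result clinically. As planned, they are less precise than the data allow and more exposed to chance baseline imbalance than the primary estimate beside them.

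The entry rules add a second, smaller problem. A participant with nocturnal pain of 4 cm and an overall 24-hour average of 3.0 cm or less passes the baseline check. That person is then counted in the acceptable state at T1 by staying where he or she was. If there are several such people, the reported proportion mixes reaching the state with having been in it from the start.

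**Working it through.** **1. The plan's own figure.** SD 2.0 cm, difference 1.0 cm, two-sided 5% and 80% power (section 2.6) give 63.8 per group by the two-sample t calculation, so 64. Then 64/0.85 = 75.3, so 76 per group and 152 in total. This reproduces and is not in question. The document gives no figure for the responder outcomes and no baseline VAS distribution, so what follows rests on stated assumptions.

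**2. How much baseline explains.** Assume baseline SD 1.5 cm, T1 SD 2.0 cm and baseline-to-T1 correlation r. The slope of T1 on baseline is b = r × 2.0/1.5, and the residual variance is 4(1 − r²).

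- Score underlying the ≤3.0 cm outcome: share explained = r².
- Change underlying the 1.4 cm outcome: share explained = (1 − b)² × 2.25 / [(1 − b)² × 2.25 + 4(1 − r²)].

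| r | b | ≤3.0 cm | 1.4 cm fall |
|---|---|---|---|
| 0.3 | 0.40 | 0.09 | 0.81/(0.81 + 3.64) = 0.18 |
| 0.5 | 0.67 | 0.25 | 0.25/(0.25 + 3.00) = 0.08 |
| 0.6 | 0.80 | 0.36 | 0.09/(0.09 + 2.56) = 0.03 |

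These shares refer to the continuous scores. Dichotomising loses part of the gain. The pattern is clear: as r rises, baseline matters more for the state and less for the change.

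**3. Variance of the risk difference.** In simulated trials (64 per arm, true difference 1.0 cm), the variance after standardisation from a logistic model with baseline VAS, divided by the unadjusted variance, was:

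| r | ≤3.0 cm | 1.4 cm fall |
|---|---|---|
| 0.3 | 0.95-0.98 | 0.85-0.90 |
| 0.5 | about 0.85 | about 0.95 |
| 0.6 | 0.75-0.79 | 0.98-1.01 |

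The saving is therefore roughly 2-25% and about 0-15%. The mean risk difference was essentially unchanged.

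**4. Power and type I error.** With baseline mean about 5.5 cm, SD about 1.5 cm and a mean fall of 2 cm, power for the ≤3.0 cm outcome at r = 0.3, 0.5 and 0.7 was 0.58, 0.60 and 0.58 by chi-square, against 0.63, 0.67 and 0.77 by logistic regression. For the 1.4 cm fall the two tests were about equal (0.51 and 0.53; 0.65 and 0.64; 0.79 and 0.78). With no true difference, rejection rates were about 0.03-0.07 over 1,000 runs for both methods, consistent with 0.05.

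**5. Participants already at ≤3.0 cm at T0.** Assume overall VAS with mean 5-6 cm, SD 1.5-1.8 cm and screening-to-T0 correlation 0.60-0.85, and read the screening criterion as overall VAS.

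- Conditioning on screening above 3 alone: 1.2-8.8% are at or below 3.0 cm at T0.
- Adding the T0 requirement of resting or nocturnal pain ≥3 cm (correlation with overall VAS assumed 0.7): 1.1-6.8%. That is 0.011 × 152 = 1.7 to 0.068 × 152 = 10.3, or about 2-10 people.
- Wider assumptions (mean 4.5-6.5, SD 1.5-2.0, screening-to-T0 correlation 0.6-0.8), with the same gate: 0.6-11%, or about 1-17 of 152.

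The baseline component check narrows the gap but does not close it, because it uses a different item.

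**The case against.** The strongest reply is that nothing confirmatory rests here. The analyses are labelled exploratory, randomisation makes the unadjusted comparison valid, and the planned confidence intervals already cover chance imbalance. The acceptable state is defined as a state, so counting someone who was in it at entry is correct by definition; improvement is what the 1.4 cm outcome measures. Section 2.14 also says that a detailed analysis plan will follow before database lock. On the schedule, Table 1 lists no VAS row at screening, but it does list the review of eligibility criteria there, which can cover the >3 rule.

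Most of this stands, and it limits the point to precision and interpretation. It does not remove it: the article names the tests rather than leaving them open, and the covariate is already in the data.

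A reader might infer more, in four ways that the document does not support:

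- **The tests are wrong.** They are not; type I error holds without adjustment.
- **Low baseline scores dilute the primary contrast.** Nothing shows this, and the primary model conditions on baseline VAS.
- **People starting near 1.4 cm cannot respond.** Under the assumptions above, at most about 0.4% would start below 1.4 cm (0.004 × 152 = 0.6 people), too few to support a criticism.
- **The entry threshold must change.** That would exclude patients who meet the protocol's pain-dominant definition, a trade-off for the investigators.

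**Conclusion.** The point holds as a modest improvement to an exploratory analysis. Leaving baseline out of the responder comparison costs roughly 2-25% in variance for the ≤3.0 cm outcome and about 0-15% for the 1.4 cm fall, for assumed baseline-to-T1 correlations of 0.3-0.6. The gain is worthwhile for the state outcome at moderate or higher correlation and small for the change outcome.

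The absence of a minimum overall VAS at T0 follows directly from the text. Its size does not: about 1-7% of participants, 2-10 of 152, depends on an assumed baseline distribution and on reading the screening criterion as overall VAS. The primary ANCOVA, its estimate and the sample size are not affected.

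**What to change.** 1. In section 2.13, replace the chi-square or Fisher comparison with logistic regression on group and baseline overall VAS for both outcomes. Report standardised (marginal) risk differences and risk ratios with 95% confidence intervals, so that the results stay on the scale already promised rather than becoming odds ratios.
2. Report by arm the number with T0 overall VAS at or below 3.0 cm, and add an acceptable-state analysis restricted to those above 3.0 cm at T0. The restriction uses a baseline value only, so the randomised comparison is preserved.
3. State which VAS the screening criterion in section 2.3 refers to, and reconcile it with the baseline check in sections 2.2.1, 2.3 and 2.5. Any change of entry threshold is for the investigators.

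The cost is one analysis sentence, one table row and one clarification. T0 overall VAS is already collected, and section 2.13 already allows R for supplementary work if standardisation is easier there. Items 1 and 2 can be settled before database lock even if enrolment has begun.
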